#### Implementation feasibility measures

To measure feasibility, we are examining the processes and extent of implementation, implementation costs, and sustainment. We collect process and extent data in three ways: (1) through semiannual semi-structured interviews with program staff who have been involved in the CQI meetings (i.e., program supervisors and clinicians); and (2) through surveys with the entire administrative and clinical staff that measure perceptions of CQI and organizational functioning, including readiness to change.

In the semi-structured interviews with key program staff, we are collecting information on the extent and nature of implementation of the PDSA cycle and on facilitators and barriers to implementation. We examine the extent of PDSA activity using both open- and close-ended interview questions based on an interview protocol developed to measure innovation use (Levels of Innovation Use (LOU) interview by Hall & Hord [51]). We are examining the nature of the CQI Actions through open-ended questions, and progress within the PDSA cycle through close-ended questions. To determine whether programs implement the Plan-Do-Study-Act phases, we are coding how many of the stages of the PDSA cycle (0-4) and how many PDSA cycles staff achieved during the intervention period. To examine facilitators and barriers to implementation, we are using items adapted from Scheier et al. [52] and Grol and Wensing’s [53] standard items for evaluating barriers and facilitators.

Through web-based staff surveys conducted every six months, we are evaluating perceptions of CQI and organizational readiness to change. To measure perceptions of CQI, we adapted Moore and Benbasat’s [54] instrument that measures Roger’s elements of diffusion. Sub-scales of this instrument include relative advantage over usual practices (5 items; α = 0.90), the complexity/ease of use (4 items; α = 0.84), compatibility (3 items; α = 0.86), observability/demonstrability (4 items; α = 0.79), and trialability of the innovation (2 items; α = 0.71). To measure organizational readiness to change we are using Texas Christian University’s Survey of Organizational Functioning (TCU SOF) instrument [49] which measures 4 domains: motivation for change, institutional resources, staff attributes, and organizational climate.

##### *CQI Costs*

We are capturing the direct and indirect costs of CQI activities using modified versions of the standardized cost instrument for drug treatment services, the Substance Abuse Services Cost Analysis Program (SASCAP™) Labor and Cost Modules. As an innovation in costing SUD treatment programs, we also are attempting to capture opportunity costs, that is, the activities forfeited to conduct CQI activities. Specifically, our costing strategy captures the following: Direct cost – the direct expense outlay to accomplish given CQI activities; Indirect cost – the amount of time, effort and other organizational resources spent, but not as a direct cash outlay, for CQI activities; and the Opportunity cost – the net benefit of the activities foregone. The costing approach is based on the principle of Activity-Based Costing (ABC), using the data collection tools and interviews with staff members to define staff activities involved in the additional CQI intervention activities, and asking staff how they allocate their time to these activities and then in turn to products and services.

We modified the SASCAP Labor- and Cost-Modules for non-methadone outpatient services [55,56] to include aspects of residential services for those sites. Furthermore, unlike the focus of SASCAP, which is on the overall cost of one treatment program, the CQI project involves a large range of activities of varying time expended. As such, we are implementing a monthly cost questionnaire to more accurately attribute time spent on CQI activities and materials purchased rather than relying on reports at less frequent intervals.

The annual cost data collection tool includes the following: General information about the clients served including census, capacity, and length of stay; information about average salaries and number of employees, by category of personnel; capital expenses for the program, organized by category – including equipment, materials and infrastructure improvements (if any); and recurrent operational expenses used for client care, organized by category – including equipment, office supplies and utilities. Given the data systems in place and the need to reduce reporting burden, we designed a ‘corporate’ and ‘program’ version, each with unique questions. Facility program directors and a corporate compliance officer meet with a cost study analyst to input data for each cost line item using administrative, financial data. The annual cost questionnaire is filled out for the year prior to CQI (baseline) and during the year of CQI, allowing for analysis as to whether CQI affected other costs indirectly.

The monthly questionnaire collects: a) Information about man-hours spent by category of personnel and CQI activity; and b) Recurrent operational expenses used for CQI activities specifically, organized by category – including equipment, office supplies, and utilities. In the CQI trial, program staff are advised to keep in mind the CQI activities that they and other staff at their site perform. During each monthly CQI meeting, program staff recall those activities and fill out the questionnaire regarding time spent and materials purchased over the last month as a direct result of engaging in CQI.

##### *Sustainment*

To assess whether CQI activities are sustained, we plan to examine data collected from Cohort 1 during the Phase 1 implementation interviews and again during the Phase 2 period when the Cohort 1 programs are no longer receiving the intervention. These data will inform us about which CQI activities are sustained in Cohort 1 (if any), and about facilitators and barriers to sustainment. To collect these data, we are building upon the semi-annual implementation interview protocol in two ways. First, during the last set of Cohort 1 interviews, we are asking program staff about their plans to sustain CQI. Second, during the Cohort 2 intervention period, we are asking Cohort 1 staff whether the different components of the intervention are continuing, that is, whether regular CQI meetings are taking place.

### Analytic methods

The randomization of programs to study conditions is necessary given the CQI intervention is intended to change program-level practices. However, it is important to assess the effect of the multilevel study design on the statistical power to detect intervention effects [57]. One key component of the power calculations is the intra-cluster correlation (ICC), which is the proportion of the overall variance in the outcomes that is attributable to program membership. For a given sample size, statistical power decreases as ICC increases. We therefore present below our analytic approach for the analysis of each outcome, and note for which outcomes we expect to have sufficient statistical power to examine, based on ICC data from previous studies.

#### Intervention efficacy

The first set of analyses will focus on examining the effect of the CQI intervention on staff outcomes relative to the control condition (Aim 1). The hypotheses related to staff outcomes are that staff participating in the CQI intervention will demonstrate improvements in: a) job morale, b) job satisfaction, and c) attitudes towards EBPs as compared with staff assigned to the control condition. Improvement will be measured as the difference between pre-intervention and post-intervention (i.e., end of Phase 1) assessments. Improvement in staff-level outcomes will be modeled using linear multilevel regression modeling, controlling for baseline values of job morale (a), job satisfaction (b), and attitudes towards EBPs (c) when modeling those outcomes. The multilevel model structure will account for the similarity, or intra-cluster correlation (ICC), among staff outcomes within the program. The statistical significance of a dichotomous predictor of participating in the CQI intervention and its direction will be examined to test these hypotheses. We will also examine whether programs that participate in the CQI intervention experience lower staff attrition than programs assigned to the control condition (d). Given the sample size of programs in the study, we will use descriptive statistics to examine whether staff attrition is lower for staff participating in the CQI intervention.

For analyses of the staff-level outcomes (a-c)*,* we assume an intra-cluster correlation (ICC) of 0.040 for staff-level outcomes, which is obtained by averaging ICCs for data on similar measures from two external studies. One ICC estimate is from staff attitudes toward implementing ‘Getting To Outcomes,’ a site-level intervention that incorporates CQI and other elements to increase organizational evaluation capacity [58]. Other ICC estimates are for subscales from the Organizational Readiness for Change (ORC) instrument [49] that was implemented at four SUD treatment program sites from same organization participating in a prior RAND study [59]. We will have 80% power (alpha = 0.05, two-sided test) to detect an effect size of 0.63 standard deviations (SDs). Our analyses of staff attrition (d) will be limited to exploratory analyses given the lack of statistical power for formally testing whether CQI has an effect on attrition.

The second set of analyses will focus on client outcomes. As most client-level outcomes are reported dichotomously, we will fit for most outcomes multilevel binomial regression models to test these hypotheses. Other forms of the generalized multilevel model will be used for continuous outcomes as appropriate. The statistical significance of the dichotomous predictor of being assigned to the CQI intervention will be examined.

Table 1 summarizes the power calculations for the client-level outcomes. Column 1 provides an estimate of the intra-class correlation (ICC) from the preliminary program data; column 2 shows the base rate assumed for the comparison group on each outcome available to us in preliminary program data; and column 3 shows the percentage point difference in the outcome between the intervention versus control arm (assuming it maintained the assumed base rate) that would be detectable with 80% power (alpha = 0.05, two-sided test). The arrest rate outcome is not presented in this table, as its base rate is too low and ICC too high to yield an outcome for which we would have sufficient statistical power to detect meaningful effects.

**Table 1 T1:** Percentage point difference detectable assuming control group base rate and intra-cluster correlations

**Outcomes**	**(1) Intra-cluster correlation**	**(2) Base rate (for control arm)**	**(3) Percentage point difference detectable**
Length of stay > 90 days	0.008	50.0%	10.7
Satisfaction:% rating treatment experience as ‘Very Good’	0.110	52.0%	24.0
% giving counselor a 'Very good’ rating	0.038	78.0%	11.4
Positive compliance	0.002	60.0%	6.6
% weekly or more frequent substance use*	0.048	10.9%	8.3
Employed or in school*	0.150	64.4%	26.0
Positive employment activities*	0.010	16.0%	7.2
Emergency medical care*	0.009	8.2%	4.2
Attended self-help groups*	0.008	75.4%	6.9

*****Measured at baseline and follow-up. The power calculations reflect the assumption that the correlation between baseline and follow-up observations of the same measure is 0.7 and that the baseline measure is a covariate in the analytic model.

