## Methods/Design

### Study site and participants

The study site is a non-profit SUD treatment provider in Los Angeles County that receives a mix of public and private funding. Nonprofit providers represent the largest proportion (61%) of SUD treatment programs nationally (as compared to for-profit [27%] and public [12%] programs) [39]. Consistent with recommendations for a collaborative approach to organizational change and to CQI, the Director of Quality Assurance of the provider organization is a co-Principal Investigator on the study.

We selected eight of the organization’s SUD treatment programs to participate in the study. The eight programs represent typical publicly funded addiction treatment programs in Los Angeles County. We included four residential and four outpatient programs that are relatively close in size and budget. The programs each serve on average 197 (residential) or 320 (outpatient) diverse clients (i.e., 60% male; 26% White, 29% African American, 40% Hispanic, and 5% Asian and/or other) annually. Average length of stay ranges from 85 to 115 days in residential and outpatient treatment, respectively.

Although assignment to the CQI intervention is at the program level, participants at multiple levels participate in intervention activities. Specifically, onsite meetings with clinical and administrative staff at each of the participating programs are planned after random assignment so that all clinical and administrative staff are directly informed about the project. In addition, one supervisor and one member from the clinical team from each program assigned to the intervention are asked to attend monthly CQI meetings held at the organization’s headquarters with the other assigned program staff. The staff that attend these monthly CQI meetings are responsible for bringing information back to their respective programs. Other clinical and administrative staff at the sites are involved in the evaluation component of the study.

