### Study design

The study is a group-randomized trial (GRT). Eight programs, stratified by modality (residential or outpatient), are being randomly assigned to receive the intervention either during the first study phase (these programs comprise ‘Cohort 1’) or the second (Cohort 2) (see Figure 1).

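### Table 1's detectable differences for the two satisfaction outcomes (24.0 and 11.4 points) do not follow from their printed ICCs and base rates with four programs per arm

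*Protocol article*

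**What the plan says.** Under Study design, the protocol article states: "Eight programs, stratified by modality (residential or outpatient), are being randomly assigned to receive the intervention" in the first or the second phase. Study site and participants adds: "We included four residential and four outpatient programs". The split is therefore four programs per arm if allocation is equal within modality.

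Under Intervention efficacy, column 3 of Table 1 is the difference "that would be detectable with 80% power (alpha = 0.05, two-sided test"). Two rows concern satisfaction:

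- "Satisfaction:% rating treatment experience as" Very Good: ICC 0.110, control rate 52.0%, detectable difference 24.0 points.
- The row for clients "giving counselor a" top rating: ICC 0.038, control rate 78.0%, detectable difference 11.4 points.

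The table's footnote applies a baseline-to-follow-up correlation of 0.7, with the baseline measure as a covariate, to the starred rows. Neither satisfaction row carries a star. Analytic methods defines the ICC as the share of total outcome variance due to program. The number of clients behind each row is not given.

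**The concern.** With few clusters, the program-level variance does not shrink as more clients are surveyed. For any ICC above zero, four programs per arm impose a smallest detectable difference that no client number can beat. Both printed satisfaction differences lie below that limit when it is computed from the table's own inputs.

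Analytic methods presents these calculations as showing which outcomes have enough power to be examined. Intervention efficacy leaves arrest out of the table for lack of power but keeps both satisfaction outcomes for significance testing. A null satisfaction result would be read against 24.0 or 11.4 points at 80% power when the printed inputs give clearly less, and a later trial planned from this pilot could inherit the error.

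**Working it through.** **Inputs.** Programs per arm k = 4 (Study design; Study site and participants). ICC and control rate p1 per row (Table 1). Power 80%, two-sided alpha 0.05, so the normal multiplier is 1.960 + 0.842 = 2.802. Clients per program m is not given for any row, so it is left free and taken to infinity as the best case.

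**Formula.** With p2 = p1 + d,

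Var(difference) = [p1(1−p1) + p2(1−p2)] × [(1−ICC)/m + ICC] / k,

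which tends to [p1(1−p1) + p2(1−p2)] × ICC / k as m grows. The detectable difference solves d = 2.802 × SE.

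**Does this look like the table's method?** For the unstarred length-of-stay row (ICC 0.008, base 50.0%), take m = 258.5, the mean of the annual caseloads of 197 and 320. At d = 0.107 the SE is 0.0380 and d/SE = 2.81. The solution is d = 10.7 points, as printed. This suggests a normal-approximation calculation with four programs per arm. It does not prove that 258.5 was the figure used.

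**Power at the printed satisfaction differences, unlimited clients.**

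- Treatment experience, d = 0.24: SE = sqrt[(0.52×0.48 + 0.76×0.24) × 0.110/4] = sqrt[(0.2496 + 0.1824) × 0.0275] = 0.109. d/SE = 2.20; power = Φ(2.20 − 1.96) = 59.6%.
- Counselor, d = 0.114: SE = sqrt[(0.78×0.22 + 0.894×0.106) × 0.038/4] = sqrt[(0.1716 + 0.0948) × 0.0095] = 0.0503. d/SE = 2.27; power = Φ(2.27 − 1.96) = 62.0%.

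**Smallest difference with 80% power, unlimited clients.**

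- Treatment experience: d = 29.4 points. Check: 2.802 × sqrt[(0.2496 + 0.814×0.186) × 0.0275] = 2.802 × 0.1050 = 0.294.
- Counselor: d = 13.6 points. Check: 2.802 × sqrt[(0.1716 + 0.916×0.084) × 0.0095] = 2.802 × 0.0486 = 0.136.

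**Finite clients and small-cluster critical values.**

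| Clients per program | Treatment, normal | Treatment, t 6 df | Counselor, normal | Counselor, t 6 df |
|---|---|---|---|---|
| 50 | 31.2 | 35.9 | 16.0 | 18.3 |
| 258.5 | 29.8 | 34.4 | 14.1 | 16.3 |
| unlimited | 29.4 | 34.0 | 13.6 | 15.7 |

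The 6 df come from eight programs minus two arms. On 6 df, power at the printed differences with unlimited clients is about 46% and 48%.

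**Sensitivity to the formula, unlimited clients (treatment / counselor).** Pooled variance gives 57% / 61%; control-rate variance in both arms 54% / 52%; arcsine 58% / 62%; one-sided 0.05 71% / 73%. A simulation with beta-distributed program rates gives 60% / 62% with normal critical values. None reaches 80%.

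**What would have to differ.** By the normal method with unlimited clients, the printed differences need ICCs no larger than 0.068 and 0.025, or 6.5 and 6.1 programs per arm (seven after rounding up).

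**The case against.** The strongest reply is that a variance reduction was assumed but not disclosed for these rows. The 0.7 correlation gives a factor of 1 − 0.49 = 0.51. With it, the normal method returns 24.0 points at about 38 clients per program and 11.4 points at about 89, both plausible survey counts. The same factor at about 150 clients comes close to several starred rows, for example 7.2 for positive employment activities (printed 7.2) and 7.0 for self-help groups (printed 6.9). A program-level baseline is also conceivable: satisfaction is collected quarterly at every program, and such a baseline would act on exactly the variance that sets the floor. At 258.5 clients per program, residual ICCs of about 0.064 and 0.021 would be enough. Adjustment for modality could also remove some between-program variance.

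This stands as a possible explanation, but not as a defence of the table as printed. The footnote limits the factor to starred rows, and no program-level baseline or modality adjustment is stated for the satisfaction rows. The document does not show whether the cause is a missing star, a wrong ICC or a wrong program count. Even with the 0.51 factor and unlimited clients, power on 6 df is only about 73% and 75%. Reading the ICC on the logit scale would lift the counselor row to 93% by the normal method but treatment experience only to 66%, and it conflicts with the article's own definition of the ICC.

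Three stronger readings are tempting, and the document does not support them.

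- A reader might infer that 80% power for these differences is unattainable under any analysis. The floor assumes no covariate or stratum adjustment, so the supportable claim is that the figures do not follow from the printed inputs.
- A reader might infer that the positive-compliance row is wrong too, since 258.5 clients gives 7.3 points against 6.6 printed. The client number for that row is unknown. About 356 clients per program gives 6.6, and so, nearly, does an ICC of 0.0015 (within rounding of 0.002) with about 298.
- A reader might put fixed replacements such as 35 and 17 points into the table. Those need about 150 surveys per program, which the article does not give, and a switch to t values in only some rows.

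**Conclusion.** The point holds for the two unstarred satisfaction rows. With four programs per arm and the printed ICCs and control rates, 80% power requires at least 29.4 and 13.6 points instead of 24.0 and 11.4, and power at the printed values is at most about 60% and 62%. With 6-df critical values the floors are about 34.0 and 15.7 points and the power about 46% and 48%.

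This rests on equal allocation (an unequal split only lowers power), on the ICC as the article defines it, and on no adjustment beyond what is stated for these rows. It does not depend on the unreported client numbers.

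Severity is moderate. Study aims and hypotheses declares the hypotheses developmental and exploratory, and the eight programs were selected from one organisation, so nothing in the article ties their number to these rows. The error bears on how a satisfaction result may be read, not on whether the trial can run.

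**What to change.** Recalculate both rows with four programs per arm and the actual number of surveys per program. Without a variance reduction, the results will be at least 29.4 and 13.6 points. Preferably use small-cluster t critical values, and then for every row, so that the table stays on one basis.

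Alternatively, if a variance reduction was assumed (the 0.7 baseline correlation, a program-level baseline or a modality adjustment), state it, put that covariate in the analysis model and mark the two rows. If no such adjustment is available, the satisfaction outcomes should not be described as having 80% power for 24.0 and 11.4 points.

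The cost is a recalculation, a table edit and less favourable stated figures.

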**Methods/Design:**

A group-randomized trial using a modified stepped wedge design is being used. In the first phase of the study, eight programs, stratified by modality (residential, outpatient) are being randomly assigned to the intervention or control condition. In the second phase, the initially assigned control programs are receiving the intervention to gain additional information about feasibility while sustainment is being studied among the programs initially assigned to the intervention.

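### Table 1's two satisfaction rows state detectable differences (24.0 and 11.4 points) that four programs per arm cannot reach at the printed ICCs, however many clients are surveyed

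*Protocol article*

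**What the plan says.** The protocol article, Study aims and hypotheses, lists higher treatment satisfaction as one of four client hypotheses. Analytic methods says the power figures show which outcomes can be examined with enough power, and defines the ICC as a quantity "which is the proportion of the overall variance in the outcomes that is attributable to program membership".

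Under Intervention efficacy, column 3 of Table 1 is described as the percentage-point difference "that would be detectable with 80% power (alpha = 0.05, two-sided test"), given the ICC in column 1 and the control rate in column 2. The two satisfaction rows are:

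| Row | ICC | Control rate | Detectable difference |
|---|---|---|---|
| "Satisfaction:% rating treatment experience as" 'Very Good' | 0.110 | 52.0% | 24.0 points |
| % "giving counselor a" 'Very good' rating | 0.038 | 78.0% | 11.4 points |

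Neither row carries an asterisk. The footnote to the asterisk reads in part: "The power calculations reflect the assumption that the correlation between baseline and follow-up observations of the same measure is 0.7", with the baseline measure as a model covariate.

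On the design, the abstract states that "eight programs, stratified by modality (residential, outpatient) are being randomly assigned to the intervention or control condition", and Study site and participants adds: "We included four residential and four outpatient programs that are relatively close in size and budget". Efficacy is the Phase 1 contrast of Cohort 1 with Cohort 2 (The present study).

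**The concern.** In a cluster-randomised comparison, adding clients reduces only the within-program part of the variance. The between-program part depends on the ICC and the number of programs, and it sets a smallest detectable difference that no client sample can improve on. With four programs per arm and an ICC of 0.110, a 24-point difference looked too small to be detectable at 80% power. The counselor row raised the same doubt.

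The table is used to sort outcomes. Arrest is left out of it for lack of power, staff attrition is called exploratory and sustainment descriptive. Satisfaction carries no such caveat. If its figures are wrong, the plan claims a sensitivity it does not have, and a null satisfaction result would be read as stronger evidence against an effect than it is.

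**Working it through.** **Inputs.** Two-sided alpha 0.05 and 80% power (Intervention efficacy): 1.960 + 0.842 = 2.802. Programs per arm k = 4. This is implied by randomising four residential and four outpatient programs within modality; an unequal split would generally make matters worse. ICCs and control rates are from Table 1. The variance factor is 1 for unstarred rows and 1 − 0.7² = 0.51 for starred rows. The number of satisfaction respondents per program, m, is not given.

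**Formula.** d = 2.802 × √{[p1(1−p1) + p2(1−p2)] × [1 + (m−1)ICC] / (4m)}, with p2 = p1 + d solved iteratively. As m grows without limit, [1 + (m−1)ICC]/m tends to the ICC. The floor is therefore d = 2.802 × √{[p1(1−p1) + p2(1−p2)] × ICC / 4}.

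**Check on the table's other rows.**
- Length of stay (ICC 0.008, 50.0%), with m = (197 + 320)/2 = 258.5 clients a year: [1 + 257.5 × 0.008]/258.5 = 0.01184. Then d = 2.802 × √(0.4887 × 0.01184/4) = 10.7 points, as printed.
- With the 0.51 factor and m about 152, the formula gives 7.2 (positive employment activities), 4.2 (emergency care, taken as a decrease) and 6.9 (self-help groups), all as printed.
- The remaining rows need other values of m: about 356 for positive compliance, 116 for weekly substance use (as a decrease) and 13 for employed or in school. The formula is plausible, but the exact inputs behind the table cannot be fully recovered.

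**The satisfaction rows cannot be reproduced at any m.** The largest ICC compatible with a printed difference, with unlimited clients, is (d/2.802)² × 4 / [p1(1−p1) + p2(1−p2)].
- Treatment experience: (0.24/2.802)² × 4/0.4320 = 0.068, against 0.110 printed.
- Counselor: (0.114/2.802)² × 4/0.2664 = 0.025, against 0.038 printed.

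**Floors.**
- Treatment experience, p2 = 0.814: 2.802 × √(0.4009 × 0.110/4) = 2.802 × 0.1050 = 29.4 points.
- Counselor, p2 = 0.916: 2.802 × √(0.2485 × 0.038/4) = 2.802 × 0.0486 = 13.6 points.

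**Power at the printed differences, unlimited clients.**
- Treatment experience: SE = √(0.4320 × 0.110/4) = 0.1090; Φ(0.24/0.1090 − 1.960) = 59.6%.
- Counselor: SE = √(0.2664 × 0.038/4) = 0.0503; Φ(0.114/0.0503 − 1.960) = 62.0%.

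**Finite m.** As a range, take m = 73 (an assumed average census: 197 × 85/365 = 46 and 320 × 115/365 = 101, mean 73) up to 258, the annual number served.

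| Clients per program | Treatment experience: detectable (power at 24.0) | Counselor: detectable (power at 11.4) |
|---|---|---|
| 73 | 30.7 (55%) | 15.3 (50%) |
| 258 | 29.8 (58%) | 14.1 (58%) |
| Unlimited | 29.4 (60%) | 13.6 (62%) |
| Printed | 24.0 (80%) | 11.4 (80%) |

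**Other variance choices.** The floors are 30.8 and 13.8 with pooled variance, 32.8 and 16.0 with control-arm variance, 26.8 and 11.7 with intervention-arm variance, and 26.6 and 12.3 even with a one-sided test. A t reference with 6 df raises them to 33.9 and 15.7. On the arcsine scale the printed effects are 0.507 and 0.313, where 0.657 and 0.386 are needed. Every choice leaves the printed figure below the floor. To reach the printed figures with unlimited clients would take 6.48 and 6.11 programs per arm, so seven.

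**With the 0.51 factor.** The floors fall to 22.1 and 10.2, and the printed values are met at m of about 38 and 89.

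**The case against.** The arithmetic on the printed inputs is not in dispute. The arguments against the finding are these.

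- *ICC scale.* The client models are multilevel binomial, where a latent-scale ICC is common. On the logit scale the counselor floor is 9.9 points and 11.4 is attainable; the treatment-experience floor is still 27.3. The article's definition, a share of overall outcome variance, favours the outcome scale, and the length-of-stay row reproduces on it. The counselor row is nonetheless the less secure of the two.
- *Adjustment for modality.* If the printed ICC includes residential–outpatient differences, adjusting for stratum would lower it. With unlimited clients, modality would have to absorb 1 − 0.068/0.110 = 38% (treatment experience) or 1 − 0.0249/0.038 = about 35% (counselor) of the between-program variance; at m = 73, about 50% and 70%. The article states no such adjustment.
- *A baseline could exist.* Quarterly surveys at all programs could supply a program-level baseline. But the surveys cover whoever attends that week, no client-level baseline is described, and the footnote does not extend the credit to these rows. A missing asterisk is a possible cause of the figures; it would still be an error in the table.
- *Replacement values rest on an assumed m.* This stands. Only the floors follow from the document.
- *Exploratory pilot.* The hypotheses are described as exploratory, and nothing shows that Table 1 set the sample size. That limits the consequences, but it does not make a claim of 80% power correct where the design gives 60% or so at best.

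**Conclusion.** The concern holds: both cells are wrong as written. With 4 v 4 programs, the printed ICCs and control rates, two-sided alpha 0.05 and no covariate credit, the smallest differences detectable at 80% power are 29.4 points (printed 24.0) and 13.6 points (printed 11.4), before any small-cluster correction. A true 24-point gain in treatment experience would be missed at least 40% of the time, where the plan implies 20%.

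The result does not depend on the unknown number of respondents. It does assume that the ICC is a share of outcome variance, as the article defines it, and that the analysis is not adjusted for modality or a baseline. The treatment-experience row also fails on the logit scale; the counselor row would not.

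**What to change.** Choose one of two corrections and state the number of respondents per program used.

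1. Without baseline credit, restate the cells. For 73 to 258 respondents per program they are about 30–31 points (treatment experience) and 14–15 points (counselor), and in no case below 29.4 and 13.6. Say whether a small-cluster correction is included.
2. If baseline credit was intended, star both rows, put the covariate in the analysis model, and give the program-level correlation that justifies it, since a client-level correlation of 0.7 is not available from a survey of whoever attends.

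In either case, state the ICC scale and whether modality is adjusted for. If treatment experience is restated at about 30 points, label it descriptive, as the plan already does for staff attrition and sustainment. The cost is two table cells and about one sentence, with less favourable figures; assignment and outcomes do not change, and the analysis model changes only under the second option.
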